Ideally, we would like to know the drug level just prior to a detectable parasitemia in the participant since at that level, parasites were able to begin to replicate. Since it is impossible to anticipate when a new patent parasitemia will occur, we will attempt to predict the level retrospectively by obtaining the pharmacokinetic curve in the population. We will also measure the level at the time of recurrent parasitemia in case the participant was found to vary significantly from the mean.

1. Assess the effect of population movements on the risk of malaria infection.

- Risk of malaria in children who traveled outside the city compared to those who did not.

Our interest is the first incident of malaria. Malaria illness will be defined as any level of microscopy-confirmed *Plasmodium falciparum* parasitemia accompanied by signs or symptoms consistent with malaria either leading to treatment-seeking behavior or reported during follow-up visits. This definition is more inclusive since practicing physicians in a malaria endemic area would treat a person who presents complaining of illness and who had documented parasitemia. This definition will enable the longitudinal study to capture all first episodes of malaria illness that would be treated under standard medical practice. Time to malaria illness after baseline is defined as number ofdays without malaria illness after baseline up to the date of the first illness. Dates will be recordedfor all the events occurring prior to or during follow-up.

1. Assess the spatial patterns and the environmental determinants of malaria infection

- Distribution of malaria cases in relation to environmental factors in Ndirande.

In order to evaluate whether there is clustering of cases and/or spatial correlation with environmental variables, we will carefully analyze the spatio-temporal pattern of all cases. All new malaria illnesses after the initial treatment will be escorted home and their location geo-referenced using GPS. Information will be entered into ArcGIS (*ESRI, Redland, CA*) to create a spatial point pattern. This will be linked to the database with information on health, demographic, economic, social, ecological and agricultural characteristics.

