### Cases of malaria during follow-up period

If symptomatic malaria recurs within 14 days of the initiation of study treatment, rescue therapy will be given and the episode will be coded as an early treatment failure or late clinical failure. If an illness episode occurs more than 14 days after the initiation of the last treatment, it will be considered to be a new clinical episode and treated with the study drug. The case definition of uncomplicated malaria for new clinical episodes is a positive malaria smear and any of the following signs or symptoms:

- Fever measured at the clinic
- History of fever in the past 24 hours
- Vomiting
- Abdominal pain
- Poor oral intake
- Headache
- Irritability for at least 12 hours

Any participant who has danger signs or signs of severe disease (as described above) including a parasite density greater than 10% or greater than 500,000/mm3 will not be treated with the study drug and will be transported to Queen Elizabeth Central Hospital for further management.

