## Sample Size Considerations

In a previous longitudinal study of malaria in this population, we found that the mean annual incidence of malaria was approximately 2.5 episodes per year (59) with a standard deviation of approximately 2. Chloroquine is presently highly effective in treating malaria and has a prolonged prophylactic effect, so we have estimated a mean rate of 1.5 malaria episodes per year with chloroquine alone. We derived the sample size required to detect a decrease in the mean to 1.0 episodes per year assuming a Poisson distribution and using a 2 sided test with alpha= .05/3=.0166. The test size was adjusted to accommodate the 3 treatment versus control comparisons. With the above requirements and for a 2 treatment contrast, 120 subjects with complete observation are required per treatment arm to have 90% power (PASS 2005). To account for migration and other causes of attrition, we will enroll an additional 33% (40 subjects) in each regimen. We will accrue 160 per arm for a total of 640 subjects.

Because of the currently estimated efficacy of chloroquine alone in Malawi (in excess of 95%), we are unlikely to determine differences in initial administration (day 28) efficacy between the treatment arms. Power is limited as all arms should have very few early failures. Rates of anemia (<8 mg/dl) at the end of one year should be available in ~120 subjects per arm. The 95% CI half-width for the difference in anemia rates, calculating the variance with a rate of .2, is approximately .10. Thus, the selected sample size should be informative about larger treatment arm differences in anemia rates.

To determine the population pharmacokinetic curve for chloroquine, we have designed a randomized unbalanced study. All participants will have chloroquine levels determined prior to drug administration, at day 14 and at one additional randomly assigned time point. The assignment will be weighted to increase measurement on day two. Planned Interim Analyses

The DSMB will decide when it would like to conduct the interim analysis. The data to be reviewed at this meeting will include safety and efficacy data.

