Spatial Cluster analysis will be used to identify an unusually high occurrence of morbidity that is clustered in space and time. In order to identify disease clusters in smaller areas located near a potential high risk factor (putative source: ponds, rivers, water pools, streams, swamps), focused spatial cluster analysis will be carried out to assess the presence of a statistically significant grouping of cases. A number of methods exist to reveal clusters of high and low malaria rates observed during the study period. Here we propose use of Kulldorff’s SaTScan statistic**.** SaTScan uses a replication method to create a spatial scan statistic by imposing a circular window, which is then centered around each of several possible centroids positioned throughout the study region. For each centroid, the radius of the window varies continuously in size from zero to an upper limit, thus creating an infinite number of distinct geographical circles, each being a possible candidate for a cluster. In addition, a recent local indicator of spatial autocorrelation (LISA), Getis G*i, statistic, will be used to detect hotspots of malaria illnesses and relate them to putative sources of malaria transmission *.*Gi* measures spatial association by using distance under the assumption that the variable has a natural origin, and would supplement the Kulldorff’s SaTScan.

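### If the spatial scan is run as a Poisson case-count scan on all episodes, repeat malaria in the same child can pass for clustering by place (secondary objective 8)

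*Protocol*

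**What the plan says.** Only the protocol was available for this point.

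- Secondary Outcome Measures (3.2.2), objective 8, sets the scope: "we will carefully analyze the spatio-temporal pattern of all cases". On the data it says: "All new malaria illnesses after the initial treatment will be escorted home and their location geo-referenced using GPS". The locations then go into a geographic information system "to create a spatial point pattern".
- Cases of malaria during follow-up period (7.3.1) says of an illness starting more than 14 days after the last treatment began: "it will be considered to be a new clinical episode and treated with the study drug". One child can therefore contribute several points at one address.
- Spatial analysis (under 11.3) gives the aim: "Spatial Cluster analysis will be used to identify an unusually high occurrence of morbidity that is clustered in space and time". It names Kulldorff's scan: "SaTScan uses a replication method to create a spatial scan statistic by imposing a circular window". For each centre, "the radius of the window varies continuously in size from zero to an upper limit". The section speaks of finding places where malaria rates are high or low, and of testing whether groups of cases near water are statistically significant.
- Sample Size Considerations (11.2) gives the earlier incidence in this population as "approximately 2.5 episodes per year (59) with a standard deviation of approximately 2".
- The travel objective, also in 3.2.2, is limited to a child's first malaria illness. Objective 8 has no such limit.

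**The concern.** Objective 8 asks whether malaria risk depends on where the house is, so the relevant null is that location does not matter. For case counts, the usual scan reference distribution drops each case independently onto the population at risk. That null is stricter: it also says that no child is more prone to malaria than another.

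If some children are ill more often for reasons unrelated to place (age, immunity, bed net use), their episodes stack on one point. Because windows grow from radius zero, a small circle around one or a few such children can exceed the critical value. The protocol then relates detected hotspots to ponds, streams and other putative sources, so a false cluster could be read as an environmental effect.

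**Working it through.** **1. The plan's own figure.** The protocol states no error rate for the scan. Its only computed figure built on the episode rate is 120 complete children per arm (1.5 versus 1.0 per year, Poisson, two-sided alpha 0.05/3, 90% power). The Poisson-regression formula gives N = [z(1−α/2)·√4 + z(0.90)·√5]² / (1.5·ln(1/1.5)²) = 237.5, or 118.8 per arm. The figure is reproduced to within one child. This confirms how the rates are meant; it does not bear on the scan.

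**2. Overdispersion implied by 11.2.**
- Variance 2² = 4; variance/mean 4/2.5 = 1.6.
- Between-child CV² = (4 − 2.5)/2.5² = 0.24, if all the excess is stable, non-spatial difference between children.
- Expected mean in this trial if every combination arm reaches its target: (1.5 + 1.0 + 1.0 + 1.0)/4 = 1.125. The same CV² then gives variance/mean 1 + 0.24 × 1.125 = 1.27.
- If the historical SD were 1.75 (an assumption, to show sensitivity): CV² = (3.0625 − 2.5)/6.25 = 0.09.

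**3. Simulation with no spatial effect.** Assumptions: a Poisson scan for high clusters, 5% level, windows up to 50% of children, one child per house, full-year follow-up, and gamma-distributed differences between children that are independent of location. Base case: 480 children (4 × 120), mean 1.125. The ranges pool separate runs that differ in number of null data sets and simulated layout.

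| Setting | Data sets with a false cluster |
|---|---|
| Poisson counts, no child differences (calibration; some runs at mean 1.5 or with 640 children) | 3–6% |
| CV² 0.24, windows centred on every house | 30–40% |
| Same, mean 1.0 | 27% |
| Same, windows of at least 5 children | 22–27% |
| Same, windows of at least 10 children | 22% |
| CV² 0.24, centres on a regular grid | 19–21% |
| CV² 0.24, ten fixed centres | 16% |
| CV² 0.24, house centres, all 640 children for a full year | 43.5% |
| CV² 0.09 | 6–10% |
| Arm rates 1.5/1/1/1, no other differences (480 / 640 children) | 8% / 10% |

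In overdispersed settings the median false cluster held 2 to 6 children, and 50–71% of false clusters held five or fewer. That fits the mechanism.

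**4. Spacing of episodes.** With a protected interval after each treatment, and child differences refitted so that the historical mean of 2.5 and SD of 2 still hold (all intervals are assumptions; house centres):
- historical interval 14 days: 10.5% with a 28-day interval in this trial, 3.5% with 42 days;
- historical interval 28 days: 35% with 28 days, 13% with 42 days, 6% with 56 days.

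**5. The remedy.** In the overdispersed settings, one yes/no outcome per child gives 2.0–5.2% false clusters. Permuting whole child counts over the houses gives 3.5–7.0%. Both agree with 5% within simulation error.

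**The case against.** The strongest reply is that the protocol does not fix the faulty analysis. It names no probability model, reference distribution, maximum window or level, and it never says that episodes are independent. It speaks of clustering in time as well as space. A space-time permutation model conditions on each location's total and would largely remove the effect. Such choices commonly sit in an SAP. This stands as far as the model goes, so the point is conditional on a Poisson scan. It does not dispose of the input: 3.2.2 sets all cases as the data for objective 8, although the same section limits the travel objective to first illnesses.

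The size is also open to challenge, and this largely stands:
- The protocol refers to several centres placed across the region, not to every house. Fewer centres lower the rate.
- The historical figures are approximate and come from a trial of other drugs. Their spread may include real spatial variation, age and unequal follow-up.
- Sample Size Considerations expects a prolonged prophylactic effect from chloroquine, and the Pharmacokinetics table gives activity for up to 70 days. Spacing of this kind pulls counts towards Poisson.

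A reader might infer that a third or more of null data sets would show a cluster. The figures do not support that as a general statement: 16–27% is as plausible as 30–40%, and lower values are possible. A reader might also infer that the Getis Gi* analysis shares the fault. That was not tested, and Gi* is standardised by the observed variance of the values rather than by this Poisson reference.

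**Conclusion.** The point holds in conditional form. With all episodes as points and a Poisson scan, non-spatial differences between children inflate the false-cluster rate. If CV² is about 0.24 and none of it is spatial or due to follow-up, the rate at a nominal 5% is roughly 15–40%, depending on centres, minimum window and mean rate (43.5% in the extreme case of all 640 children followed for a full year). It can fall to about 5–10% if CV² is nearer 0.09 or if post-treatment protection spaces episodes out. The documents do not settle which applies.

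Higher figures can be produced: 67–75% if the variance/mean ratio of 1.6 carried over to the lower rate. That would need CV² = 0.6/1.125 = 0.53, more than twice what the history gives, so I do not rely on it.

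Nor would objective 8 necessarily be answered wrongly as a whole. The plan also has a river-proximity covariate, a focused analysis at putative sources and Gi*. The primary endpoint, sample size, treatment comparisons and safety analyses are untouched. This is a worthwhile improvement to one secondary objective.

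**What to change.** In the spatial analysis section, name the scan's probability model and make the child the unit, in one of two ways:

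- one outcome per child: any new episode versus none, or time to first new episode; or
- all episodes kept, with the reference distribution built by permuting each child's whole record (episode count and person-time) over the house locations.

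No new data are needed, because Enrollment/Baseline (7.2) already records the house location of every enrolled child. The first option loses some power for true clusters because repeat episodes are set aside. The second keeps them and costs a small amount of programming. Either needs about one sentence in the protocol or SAP.

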# Objectives

## Study Objectives

The primary objective of this study is to compare the annual incidence of malaria.

Secondary objectives are:

1. Assess the antimalarial drug efficacy at first administration, by treatment arm.
2. Assess the antimalarial drug efficacy during subsequent episodes of malaria, by treatment arm.
3. Measure the prevalence of chloroquine resistant parasites during the trial, by treatment arm.
4. Assess the effect of each treatment arm on anemia at the end of study participation.
5. Assess the safety of repeated use of the drugs in each of the study arms.
6. Determine the chloroquine blood levels at which chloroquine sensitive and resistant parasites are able to cause infection.
7. Assess the effect of population movements on the risk of malaria infection
8. Assess the spatial patterns and the environmental determinants of malaria infection

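### The spatial analysis promises a focused analysis of malaria near water, but the scan it describes is a general one and does not test that question

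*Protocol*

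**What the plan says.** Section 3.1 of the protocol lists, as the last of eight secondary objectives, "Assess the spatial patterns and the environmental determinants of malaria infection". Section 3.2.2 gives two aims under it: "In order to evaluate whether there is clustering of cases and/or spatial correlation with environmental variables".

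The Spatial analysis part of section 11.3 then does three things.

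- **It sets a source-specific question.** The purpose is stated as "In order to identify disease clusters in smaller areas located near a potential high risk factor", with ponds, rivers, water pools, streams and swamps listed as the putative sources. The text continues that "focused spatial cluster analysis will be carried out to assess the presence of a statistically significant grouping of cases".
- **It proposes a method.** "Here we propose use of Kulldorff’s SaTScan statistic". The scan uses windows of circular shape, and the text says of the window, "which is then centered around each of several possible centroids positioned throughout the study region". Its size may be anything up to a maximum that is not given.
- **It adds two related elements.** The Gi* statistic is to find hotspots, which are then to be related to putative sources; how is not stated. Buffer layers around water are to identify how close houses lie to it, and the share of buffer area in a village is to serve as a proximity covariate. No model is named for that covariate.

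**The concern.** A focused cluster analysis takes the suspected sources as given and asks whether risk is higher near them. A general scan searches the map for the most unusual circle and asks whether any cluster exists. The protocol states the first question and describes the second method. As described, the centroids are spread over the region and the water features do not enter the hypothesis.

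Two consequences follow.

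- **Interpretation.** Rejecting the scan's null supports a cluster somewhere. It gives no error-controlled statement about water, and a hotspot chosen from the data and then related to a nearby stream does not supply one.
- **Power.** The scan's critical value pays for searching every centre and radius, and circles fit a stream or several scattered ponds poorly. A modest excess near water may therefore go undetected where a focused test would find it.

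At stake is the environmental-determinants part of objective 8. The randomised comparison is not involved.

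**Working it through.** The protocol states no power, alpha or effect size for the spatial analysis, so there is no figure to reproduce. The check has a logical part and a numerical part.

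**1. Question against method**

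| Element | Focused analysis needs | Section 11.3 describes |
|---|---|---|
| Null hypothesis | No excess near listed sources | No cluster anywhere |
| Centres | At the sources, or distance to them | Centroids throughout the region |
| Role of water features | Part of the test | Not used in the scan |

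This mismatch does not depend on any assumed number.

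**2. Inputs from the protocol (section 11.2)**

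- Rates: 1.5 episodes per year on chloroquine alone and 1.0 under the alternative for each combination. Mean = (1.5 + 3 × 1.0)/4 = 1.125.
- Children: 640 enrolled; 4 × 120 = 480 with complete observation.
- Expected episodes: 480 × 1.125 = 540, or 640 × 1.125 = 720.

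**3. Assumptions not in the protocol**

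Homes at random in a square; one winding stream or 12 ponds; 10–30% of children near water; rate ratio (RR) 1.3–2.0; no extra-Poisson variation. The scan used 256 centroids and windows up to 50% of children. Its 5% critical value came from 1,000 null replicates, and each scenario had 400 replicates. The comparator was a one-sided 5% test of episodes inside against outside the water buffer.

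**4. Power when risk really is raised near water (scan v focused)**

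| Setting | RR 1.3 | RR 1.5 | RR 2.0 |
|---|---|---|---|
| Stream, 10% of 480 children | 7% v 68% | 11% v 92% | 42% v 100% |
| Stream, 20% of 480 | 10% v 81% | 25% v 100% | 78% v 100% |
| Stream, 30% of 640 | 19% v 94% | 49% v 100% | 98% v 100% |
| 12 ponds, range over the same three | 7–17% v 69–95% | 11–36% v 90–100% | 50–93% v 100% |

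Hand check of the focused test (20% of 480, RR 1.3). The share of episodes in the buffer is 0.2 × 1.3/(1 + 0.2 × 0.3) = 0.2453. Excess = 540 × (0.2453 − 0.2) = 24.5. Null SD = √(540 × 0.2 × 0.8) = 9.30; SD under the alternative = √(540 × 0.2453 × 0.7547) = 10.0. Power = Φ((24.5 − 1.645 × 9.30)/10.0) ≈ 82%, which agrees with the simulated 81%.

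**5. Rejection when the raised area is compact and lies off the stream**

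| Test | RR 1.3 | RR 1.5 | RR 2.0 |
|---|---|---|---|
| General scan | 12–49% | 41–94% | 96–100% |
| Focused stream test | 0–3% | 0–3% | 0–1% |

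The focused test is not proof of cause either. With the raised area at the centre of the square, or around the ponds, the stream test rejected in 4–49% of replicates. It measures association with the listed features and no more.

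**6. How far the gap depends on an accurate buffer**

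Assume about 550 child-years (550 × 1.125 ≈ 619 episodes), 12% of homes truly at risk and RR 1.3. One-sided 5% power of the near/far test was 73% with the exact buffer, 44% with a buffer holding twice the true share of homes, and 32% with three times. The scan had 11% in that setting.

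**7. Extra-Poisson variation**

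Section 11.2 cites a mean of about 2.5 episodes and an SD of about 2, so the variance of 4 exceeds the mean. A negative binomial match gives 4 = 2.5 + 2.5²/k, so k = 6.25/1.5 = 4.17. At mean 1.125 the variance-to-mean ratio is 1 + 1.125/4.17 = 1.27. A plain Poisson near/far test at nominal one-sided 5% then rejects a true null with probability 1 − Φ(1.645/√1.27) ≈ 7%. Scaling both SDs in step 4 by √1.27 gives a corrected power of Φ((24.5 − 1.645 × 10.5)/11.3) ≈ 74% instead of 82%.

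**The case against.** The strongest defence is that the scan is not the only route to the water question. Section 3.2.2 separates clustering from correlation with environmental variables. Section 11.3 also plans house proximity through buffers and defines a proximity covariate. A covariate implies a regression, and its model may properly sit in a statistical analysis plan that is not at hand. This stands against any claim that the trial cannot answer its environmental question. It does not remove the mismatch: the one analysis labelled focused and promised a significance statement is paired with a general scan, and the covariate is defined per village.

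Second, the sentence on centroids can be read as explaining how SaTScan works rather than fixing this trial's settings, since SaTScan can be run with centroids at the sources. That reading is possible, but nothing in the text says so, and the only placement described is the general one.

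Third, the power comparison favours the focused test because its buffer equals the true risk zone. This stands: step 6 shows the gap shrinking as the buffer becomes too wide, though the focused test stayed ahead in the cases examined.

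A reader might also infer that hotspots would be matched to water by eye. The protocol says only that they will be related to putative sources and does not say how, so that inference is not supported.

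**Conclusion.** The mismatch holds. The method described does not test the source-specific hypothesis it is introduced to serve, and it can be significant when water is irrelevant. That conclusion needs no assumed effect size.

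The loss of power is conditional. Over the assumed rate ratios of 1.3–1.5 the scan had 7–49% power, against 68–100% for a focused test with an exact buffer. The size of the gap depends on the share of homes near water, the layout and the buffer accuracy, none of which the protocol gives. A reader might go further and conclude that a real excess near water would usually be missed. The figures do not support that in general: at rate ratio 2.0 the scan reached 42–98%.

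The point is confined to one secondary objective. Primary, efficacy and safety analyses are unchanged.

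**What to change.** - Keep SaTScan and Gi* as exploratory, general cluster detection, and describe them as such.
- For the putative-source question, fix the list of water features from the base maps and satellite imagery before case locations are linked.
- Name one focused test of episodes per child-time by household distance, or buffer membership, to the nearest listed feature. State the distance form or buffer width in advance, since a poorly chosen buffer costs power.
- Allow for extra-Poisson variation between children: negative binomial or robust-variance regression, or a focused score test calibrated by permuting whole children. A plain Poisson near/far test would be anti-conservative on the protocol's own mean and SD.
- For point sources such as ponds, SaTScan with centroids restricted to the listed sources is an alternative.

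The cost is wording in the protocol and the statistical analysis plan. Household GPS positions (section 7.2), water layers (section 11.3, Spatial analysis) and follow-up time (section 11.3) are already planned. The one constraint is that the feature list must be settled before the case data are seen.
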